#### Recruitment, randomization, and blinding

2.3.4

The day before colonoscopy, investigators who have been trained for the study and are authorized by the principal investigator will assess candidates according to the inclusion and exclusion criteria. After eligible patients were identified, the written informed consents will be obtained from the eligible patients, their next of kin or legal representatives. At the phase, the investigators will also collect demographic and clinical characteristics data of all eligible patients, which includes sex, age, body weight, body mass index, reasons for colonoscopy, previous colonoscopy history, and comorbidity such as hypertension, diabetes mellitus, and cardiovascular disease.

All recruited patients will be randomly assigned to receive one of the 3 preparation regimes including 3 L PEG, combination of 2 L PEG and 30 mL castor oil, and combination of 1 L PEG, 30 mL castor oil, and 5 g ascorbic acid. We will generate the random sequence by using SPSS 17.0 software, and the random sequence will be sealed in opaque envelope. An independent research nurse will be designated to random all patients into 3 different groups according to the random sequence.

In order to eliminate the risk of bias as much as possible, the endoscopists will be blinded except the research nurse who conducted the randomization procedure during examine period. Moreover, we will also blind the biostatistician.

#### Study protocol

2.3.5

According to the findings from our previous meta-analysis,^[27]^ all participants enrolled in the study will be instructed to take low fat and residue diet without food color the day before colonoscopy, and all begin to fast at 20:00 pm on the day before colonoscopy. Patients can allow eating bun, bread, and chocolate in order to enhance tolerance, decrease incidence of adverse events such as hypoglycemia and cardio-cerebral vascular accidents if they experienced serious hunger feeling.

The study protocols of all 3 groups were graphically depicted in Figure 2. According to the recommendation from US Multi-Society Task Force on Colorectal Cancer,^[28]^ we will instruct all patients to ingest bowel preparation regime with split-dose. So, the 3 L PEG alone group will be instructed to ingest 1 L of PEG at 20:00 to 21:00 PM on the day before colonoscopy and the remaining 2 L at the 3:00 to 5:00 AM on the morning before colonoscopy (Fig. 2A). The combination of 2 L and 30 mL castor oil group will be instructed to ingest 1 L of PEG and 30 mL castor oil at 20:00 to 21:00 PM on the day prior to colonoscopy and the remaining 1 L of PEG and extra 1 L clean water at the 3:00 to 5:00 AM on the morning before colonoscopy (Fig. 2B). The combination 1 L PEG, 30 mL castor oil and 5 g ascorbic acid group will be instructed to ingest 0.5 L of PEG, 30 mL castor oil and 5 g ascorbic acid and extra 0.5 L clean water at 20:00 to 21:00 PM on the day before colonoscopy and the remaining 0.5 L of PEG and extra 1.5 L clean water at the 3:00 to 5:00 AM on the morning before colonoscopy (Fig. 2C). The patients were instructed to digest PEG 250 mL every 15 minutes. Moreover, all eligible participants will be admitted to take oral 10 mL dyclonlne and 20 mL clean water at the 10 minutes prior to colonoscopy. For all eligible patients, propofol injection will be intravenously administered for sedation.

**Figure 2 F2:**
[figure not shown]
Study protocol for each group. The protocol for 3 L PEG alone group was depicted in (A) protocol for 2 L PEG plus 30 mL castor oil was displayed in (B), and protocol for combination of 1 L PEG, 30 mL and 5 g ascorbic acid was delineated in (C). PEG = polyethylene glycol.

#### Rescue therapy

2.3.6

For patients with inadequate bowel preparation, direct investigators will judge whether the colonoscopy should be continued or discontinued. If the inadequate bowel preparation is not suitable for colonoscopy, patients will be instructed to prepare bowel again using the regimes freely provide by research group. Moreover, if serious side effects occur, investigators will provide quick and appropriate treatment (including drug administration), based on their medical judgement. All treatment or drug administration will be recorded.

#### Study endpoints

2.3.7

##### Primary outcome

2.3.7.1

The bowel preparation efficacy was regarded as the primary outcome, which will be assessed by using the Boston Bowel Preparation Scale (BBPS). As one of the commonest scales of assessing quality of bowel preparation,^[29]^ the BBPS evaluates right (including the cecum and ascending colon), transverse (including the hepatic and splenic flexures), and left (including the descending colon, sigmoid colon, and rectum) colon on a 4-point scoring system with a total score out of 9.^[30]^ In this scoring system, a score of 9 was summed if the whole colon was perfectly cleaned without any residual liquid, and a score of 0 was calculated if colonoscopy is impossible.^[31]^ The adequate bowel preparation was defined as having total score > 5 and no segment < 2 in the present study.^[32]^ The direct endoscopists will be trained to use the BBPS to grade the quality of bowel preparation during colonoscopy.

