##### Secondary outcomes

2.3.7.2

We will also measure the first defecation time (the endoscopists record the time of first defecation after digesting regime), the total number of defecation (the direct investigators record the number of defecation before performing the colonoscopy), the time of cecal intubation (the endoscopists record the time of starting procedure to reaching ileocecal part), detection rate of polyp and adenoma (the number of polyp and adenoma during colonoscopy), tolerance to recommended regime (the research nurse ask the patients answering the questioner with a 4-point scale), and willing to repeat the same bowel regime (the research nurse instruct the patients to answer whether they will select the same regime to perform the bowel preparation) as the secondary outcomes.

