##### Data management

2.3.7.5

All original data will be recorded in the CRF severally. The completed CRF, after signed by the direct investigators, will be transferred to the head investigator ([name]). Data entry will be doubly performed by 2 investigators using the Excel 2010. Head investigator and research nurse who is responsible for data collection, sort, and dataset construction have the right of accessing to the final trial dataset. More importantly, all process associated with data access and analysis will be supervised by the Clinical Research Ethics Committees of Chongqing University Cancer Hospital & Chongqing Cancer Institute & Chongqing Cancer Hospital.

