##### Statistical analysis

2.3.7.6

In this study, we will adopt intent-to-treat (ITT) and per-protocol (PP) method to analyze all data. Demographic and clinical characteristics will be summarized with means, medians, and standard deviations. To assess differences between groups, data will be analyzed with Mann–Whitney *U*-test, Student's *t* test and Chi-square test according to the variables evaluated. Differences between groups regarding the bowel preparation efficacy will be analyzed with the Chi-square test. We will perform the subgroup analyses according to the indication for colonoscopy and previous history of colonoscopy. It is noted that all statistical analyses will be conducted with 2-tailed test, and *P* values of < .05 will be considered as considered significant. All statistical analyses will be performed by blinded professional statisticians with SPSS ver. 17.0 for Windows (SPSS Inc., Chicago, IL).

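### More than one endoscopist produces the operator-dependent outcomes, but every named test ignores the operator; adjusting intubation time and lesion detection for endoscopist is a cheap precision gain, not the repair of a bias

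*Protocol article*

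**What the plan says.** All references are to the protocol article.

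- **Who grades the primary outcome.** Section 2.3.7.1: "The direct endoscopists will be trained to use the BBPS to grade the quality of bowel preparation during colonoscopy". The endpoint is binary: "The adequate bowel preparation was defined as having total score > 5 and no segment < 2 in the present study".
- **Other outcomes that depend on the operator.** Section 2.3.7.2 describes caecal intubation time as "the endoscopists record the time of starting procedure to reaching ileocecal part" and lesion detection as "the number of polyp and adenoma during colonoscopy".
- **Allocation.** Section 2.3.4: "We will generate the random sequence by using SPSS 17.0 software, and the random sequence will be sealed in opaque envelope". No operator factor is mentioned. The same section blinds the endoscopists to the regimen.
- **Analysis.** Section 2.3.7.6: "Differences between groups regarding the bowel preparation efficacy will be analyzed with the Chi-square test". Other outcomes get a t test, Mann-Whitney test or chi-square test, depending on the variable. The only patient factors used are the two subgroup factors, indication and previous colonoscopy.
- **Identity of the operator in the data.** The baseline items listed in section 2.3.4 include no endoscopist field. Section 2.3.7.5 says: "The completed CRF, after signed by the direct investigators, will be transferred to the head investigator".

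**The concern.** Intubation time and lesion detection can be expected to vary with the skill and habits of the person holding the endoscope, and Boston scale scores with how strictly that person grades. None of the tests named in section 2.3.7.6 can take a stratum or a covariate, so this variation is counted as unexplained patient-to-patient noise. The treatment comparisons are then less precise than the same data would allow. At stake is efficiency on the operator-dependent secondary outcomes and, to a much smaller degree, on the primary one.

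**Working it through.** **Inputs from the protocol.** Adequacy rates 85%, 90% and 95%; 255 evaluable and 282 enrolled patients (section 2.3.3); two-sided tests at P < .05 (section 2.3.7.6). The allocation ratio is not stated; 1:1:1 is assumed, giving 85 evaluable and 94 enrolled per arm.

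**Inputs not in the protocol, so assumed.** The number of endoscopists, the share of variance that they explain, and the spread of their adequacy rates. The plan has no figure of its own on operator variation to reproduce.

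**1. Intubation time (comparison of means).** If operators explain a share R² of the variance, adjustment multiplies the standard error by √(1 − R²), and the equivalent sample-size factor is 1/(1 − R²). If the adjusted comparison has 80% power, the unadjusted power is Φ[(1.960 + 0.842) × √(1 − R²) − 1.960].

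| R² (assumed) | SE ratio | SE cut | Sample-size factor | Power without adjustment |
|---|---|---|---|---|
| 5% | 0.975 | 2.5% | 1.05 | 78% |
| 10% | 0.949 | 5.1% | 1.11 | 76% |
| 20% | 0.894 | 10.6% | 1.25 | 71% |
| 30% | 0.837 | 16.3% | 1.43 | 65% |

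**2. Lesion detection.** The same mechanism applies, but the protocol gives no detection rate, so no figure is offered.

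**3. Boston scale adequacy.** The three-arm chi-square effect size at the protocol's rates is w² = [(0.05² + 0 + 0.05²)/3]/(0.90 × 0.10) = 0.0185. With 255 patients the noncentrality is 255 × 0.0185 = 4.72, which on 2 degrees of freedom gives 48% power. The stated 80% is therefore not reproduced (521 patients would be needed). That is a separate matter which operator adjustment cannot repair; 48% is used here only as the baseline.

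Simulated trials (6,000 per setting, 255 patients, unstratified allocation, random operator effect on the logit scale) gave:

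| Operators | SD of operator effect | Power, chi-square | Power, stratified Cochran-Mantel-Haenszel |
|---|---|---|---|
| 6 | 0 | 47.3% | 47.0% |
| 6 | 0.5 | 48.8% | 48.3% |
| 3 | 1.0 | 48.3% | 49.9% |
| 6 | 1.0 | 47.1% | 49.3% |

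The Monte Carlo error of a difference is about √(2 × 0.25/6000) = 0.9 points, treating the two estimates as independent. The gain is nil at SD 0.5 and about 2 points at SD 1.0. Type I error of the chi-square test was 4.4% to 5.3% across the settings with unstratified allocation.

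**4. How thin the strata are.** Expected inadequate preparations: 85 × (0.15 + 0.10 + 0.05) = 12.75 + 8.5 + 4.25 = 25.5. With four operators (assumed), the third arm has 4.25/4, about one event per operator.

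**5. Chance imbalance.** With four equally used operators and 94 per arm, the SD of one operator's share in an arm is √(0.25 × 0.75/94) = 0.0447. The SD of the difference between two arms is 0.0447 × √2 = 0.063, and 1.96 × 0.063 = 0.124, or about 12 points. If that operator's adequacy rate differed from the others' by 10 points (assumed), the contrast would move by 0.12 × 10 = 1.2 points at that extreme. The unadjusted standard error already allows for this, so it is not a second harm to be added to step 1.

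**The case against.** The strongest reply is that nothing here is an error. An unadjusted test after unstratified randomization is valid, the size of the gain rests entirely on assumptions, and covariate adjustment is often left to the analysis plan, which is not shown. The validity and the dependence on assumptions both stand. The last part stands only in part: section 2.3.7.6 does not leave the tests open but names them, and none can use the operator. Choosing a more efficient analysis is therefore a comment on a stated choice.

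Stronger readings are tempting, and the documents do not support them:

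- *Operators could bias the comparison.* A reader might infer this from the endoscopist grading his or her own procedure. Section 2.3.4 blinds endoscopists and allocates at random, and the simulated type I error is kept. For the same reason, training in the scale is not the only safeguard.
- *The primary comparison is materially weakened.* At most about 2 points of power are at issue, from a large assumed operator spread.
- *The operator can already be read off the signed case report form.* Section 2.3.7.5 speaks of direct investigators. Section 2.3.7.2 gives separate recording tasks to endoscopists and to direct investigators, so the signatory need not be the operator.
- *Allocation should have been stratified by operator.* That requires the operator to be fixed before randomization, which the protocol does not state, and the useful gain does not depend on it.

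**Conclusion.** The point holds as a cheap improvement. The planned tests are sound, but for caecal intubation time, and in direction for polyp and adenoma detection, they discard precision that a recorded operator code would recover. The size for intubation time is 5% to 43% in equivalent sample size, conditional on operators explaining 5% to 30% of its variance; at the low end it is hardly worth noticing. For Boston scale adequacy the gain is too small, and the events per operator too few, to justify replacing the primary test. The point also presumes that the plural used for endoscopists means that several take part. If one person did every procedure, it would fall away.

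**What to change.** 1. Add a coded endoscopist identifier to the case report form and the dataset.
2. Before unblinding, prespecify that intubation time and polyp and adenoma detection are compared with models that include endoscopist as a factor, with a rule for pooling operators who have few cases.
3. Keep the chi-square test as the primary analysis of adequate preparation. Add a three-arm generalized Cochran-Mantel-Haenszel test, stratified by endoscopist, as a sensitivity analysis.

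The cost is one data field, a few degrees of freedom (three, if there are four operators) and slightly more analysis work. No extra patient, reader or procedure is needed, and allocation stays as it is.

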##### Secondary outcomes

2.3.7.2

We will also measure the first defecation time (the endoscopists record the time of first defecation after digesting regime), the total number of defecation (the direct investigators record the number of defecation before performing the colonoscopy), the time of cecal intubation (the endoscopists record the time of starting procedure to reaching ileocecal part), detection rate of polyp and adenoma (the number of polyp and adenoma during colonoscopy), tolerance to recommended regime (the research nurse ask the patients answering the questioner with a 4-point scale), and willing to repeat the same bowel regime (the research nurse instruct the patients to answer whether they will select the same regime to perform the bowel preparation) as the secondary outcomes.

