### Trial design and setting

2.2

This randomized, double-blind (endoscopist and assessor), single center trial with three-arm is designed to explore the potential of 30 mL castor oil in preparing bowel prior to colonoscopy. We will enroll and randomly assign all eligible candidates to receive either 3 L PEG, combination of 30 mL castor oil, and 2 L PEG or combination of 30 mL castor oil, 5 g ascorbic acid and 1 L PEG (see Fig. 1). This study will be conducted in the Departments of Gastroenterology of Chongqing University Cancer Hospital & Chongqing Cancer Institute & Chongqing Cancer Hospital in Mainland China.

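### On the natural reading, the research nurse excepted from blinding also obtains tolerance and willingness to repeat, which conflicts with the declared assessor blinding and adds an avoidable bias risk of unknown size

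*Protocol article*

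**What the plan says.** Trial design and setting (2.2) declares the blinding: "This randomized, double-blind (endoscopist and assessor), single center trial with three-arm is designed". The abstract says the same. Patients are not listed as blinded.

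Recruitment, randomization, and blinding (2.3.4) assigns the allocation task: "An independent research nurse will be designated to random all patients into 3 different groups according to the random sequence". It then says that "the endoscopists will be blinded except the research nurse who conducted the randomization procedure during examine period", and adds: "Moreover, we will also blind the biostatistician". The research nurse who randomises is the only role named as an exception.

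Secondary outcomes (2.3.7.2) names the collector of two patient-reported items. For tolerance, "the research nurse ask the patients answering the questioner with a 4-point scale". For willingness, "the research nurse instruct the patients to answer whether they will select the same regime to perform the bowel preparation". Where that section names a recorder for its other outcomes, it is the endoscopists or the direct investigators.

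**The concern.** Both answers are opinions about the regimen. How a question is put, or how a hesitant reply is recorded, can move them, and someone who knows the arm can do either without meaning to. The bias would enter when the answer is given, so blinding the statistician does not remove it and no later analysis can.

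The outcomes matter to how the results will be read. The Introduction gives poor compliance, palatability and liquid volume as causes of inadequate preparation, and it cites improved tolerability with a 1 L PEG combination as part of the motivation. The Discussion expects the results to influence prescribing. Section 2.3.4 also states the aim of removing bias as far as possible. Patients' own knowledge of their regimen cannot be designed away here; an allocation-aware collector can.

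**Working it through.** The point turns on who does what, so the main check sets the sections side by side.

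| Task | Role named | Blinded? | Section |
|---|---|---|---|
| Allocating patients | An independent research nurse | No, named exception | 2.3.4 |
| Grading BBPS (primary) | Endoscopist | Yes | 2.3.7.1, 2.3.4 |
| Tolerance, 4-point scale | The research nurse | See below | 2.3.7.2 |
| Willingness to repeat | The research nurse | See below | 2.3.7.2 |
| Analysis | Biostatistician | Yes | 2.3.4, 2.3.7.6 |

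1. Section 2.3.4 introduces one research nurse, who allocates and therefore knows the arm.
2. Section 2.3.7.2 refers to the research nurse with a definite article and does not distinguish that person from the one in 2.3.4.
3. No other section describes a second, blinded nurse or a sealed self-completed form.
4. The natural reading is therefore that the role excepted from blinding obtains both outcomes. If assessor covers the person who obtains an outcome, this contradicts 2.2.

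The documents contain no figure for interviewer influence, so there is nothing of the plan's own to reproduce. The following shows only how a shift of a given size would act on a comparison of two arms for willingness to repeat.

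Inputs: n = 282/3 = 94 per arm (or 255/3 = 85 evaluable, from the sample size section); two-sided 5%, z = 1.96 (statistical analysis section). Assumed, not in the documents: true willingness p1 equal in both arms at 70% or 80%, and a spurious shift d of 5 or 10 points in one arm, so p2 = p1 + d.

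With p̄ = (p1 + p2)/2, s0 = √[2p̄(1 − p̄)/n] and s1 = √{[p1(1 − p1) + p2(1 − p2)]/n},

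false-positive rate = Φ[(d − 1.96·s0)/s1] + Φ[(−d − 1.96·s0)/s1].

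Worked case, n = 94, p1 = 0.70, d = 0.05: p̄ = 0.725; s0 = √(0.39875/94) = 0.0651; s1 = √(0.3975/94) = 0.0650; Φ(−1.194) + Φ(−2.73) = 0.116 + 0.003 = 0.119.

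| Shift | n = 94, base 70% | n = 94, base 80% | n = 85, base 70% | n = 85, base 80% |
|---|---|---|---|---|
| 5 points | 11.9% | 14.7% | 11.3% | 13.7% |
| 10 points | 35.2% | 48.4% | 32.4% | 44.6% |

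The calculation covers binary willingness only; it does not model the 4-point tolerance scale.

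**The case against.** Several objections have force.

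- **Same person.** That one nurse does both jobs is an inference. Section 2.3.4 calls the randomising nurse independent and identifies the exception by the task performed, which could leave room for another nurse to collect outcomes. This stands as a limit. But no second nurse is described, and if there is one, a single sentence settles it.
- **Mode.** A reader might infer that the questions are put aloud in an interview. The text does not say so. A nurse who asks patients to answer a scale may simply hand over a form, which would be close to the remedy below. The mode is left open, so the risk is lower if patients already complete the form unaided.
- **Who the assessor is.** The article does not define the term. If it means only the person grading BBPS, there is no formal contradiction with 2.2, although an allocation-aware person would still be collecting subjective outcomes.
- **Patients know their regimen.** They drink visibly different preparations and are not declared blinded, so their answers are open to bias whoever asks. This is true and limits what the change can gain. It does not justify adding a second source.
- **Importance.** A reader might infer that the case for the lower-volume regimens depends on these two items. The protocol lists them among several secondary outcomes, bases its sample size on adequate preparation (85%, 90% and 95%), and uses tolerability as background motivation.
- **Direction.** Nothing in the documents suggests that the nurse favours any regimen.

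A reader might also extend the point to Data management (2.3.7.5), which refers to the "Head investigator and research nurse who is responsible for data collection, sort, and dataset construction". That section does not support the extension. Compiling entered data is not a way to change what a patient answered, the same section has CRFs signed by the direct investigators and entered twice by two investigators, and the statisticians are blinded.

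**Conclusion.** The point holds as a modest, cheaply corrected weakness. As written, the only role excepted from blinding is also the role that obtains tolerance and willingness to repeat, and on the natural reading this conflicts with the trial's assessor blinding. It rests on two inferences: that the research nurse of 2.3.7.2 is the one of 2.3.4, and that assessor includes whoever obtains an outcome.

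The added bias is a risk of unknown size and direction. A reader might take the false-positive figures as an estimate of harm; they are not, because both the shifts and the base rates are assumed. They show only that a small systematic shift is not negligible at this sample size. A reader might also infer that the primary result is compromised. It is not by this route, because BBPS is graded by endoscopists whom the plan blinds.

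**What to change.** In 2.3.7.2, state that patients complete the 4-point tolerance scale and the willingness question themselves, on a standard form returned sealed. In 2.3.4, add that the nurse who randomises does not elicit or record these outcomes. If a different nurse already collects them, say so there.

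The cost is protocol wording and one printed form. Self-completion does not in itself call for added staff, though the article gives no staffing detail. The sample size and the clinical procedures are unchanged. The downside is that some forms may come back incomplete. The change removes the collector's influence on the answers; it does not remove bias from patients knowing their regimen, and the report should acknowledge that.
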